### Description of the intervention

#### Control group

Subjects in the control group will receive standard prenatal and postnatal care that is usually offered to mothers at both study sites. At AUBMC, standard prenatal care includes prenatal classes that cover issues related to labor, delivery and breastfeeding. Women who wish to attend a prenatal session will have to self-register. After delivery, mothers are usually instructed on breastfeeding by the nurses and their pediatricians. At SGH, there are no structured prenatal classes and any education or training on breastfeeding is often done by the nurses and pediatricians in the hospital, and later during well-baby checkups.

#### Intervention group

Women in the experimental group will, in addition to standard clinical care, receive a complex intervention starting in early pregnancy till 6 months post delivery. The intervention is composed of the following elements: a) prenatal breastfeeding education to raise knowledge and awareness, b) postpartum professional lactation support to improve maternal skills and self-efficacy, c) postpartum peer (lay) support to build social support, and enhance social capital within women’s social networks. These include skill building activities for the provision of effective breastfeeding support.

#### Details of the complex intervention

1. Prenatal breastfeeding education:

a. *Antenatal classes:* Upon enrolment and signing of the written informed consent, each subject in the intervention group will be invited to attend at least one antenatal session with as many members of her family as she wishes. Those sessions are meant to be a forum to discuss breastfeeding information and to address the family’s questions. They will be offered on a scheduled basis and open to the intervention group only in order to avoid contamination with the control group. Details of the objectives, content, format and description of the antenatal class appear in APPENDIX-A. Data on socio-demographic variables, baseline breastfeeding knowledge, behavior and attitude towards breastfeeding will be collected at the beginning of each session from each subject. We will use a “Breastfeeding Knowledge, Attitude, and Behavior” questionnaire (B-KAB) that will be developed and adapted from the following validated instruments: the Iowa Infant Feeding Attitude Scale (IIFAS) [25], the Infant Feeding Intention Scale (IFI) [26], the Breastfeeding Behavior Questionnaire (BBQ) [27,28], and the Infant Feeding Knowledge Test [29]. The B-KAB questionnaire will be developed through a discussion among all investigators for adjustments before generating the first version. After reaching a consensus, two experts in breastfeeding will be asked to review the questionnaires for content validity and cultural appropriateness. It will then be translated to formal Arabic (Grade 4 literacy level) by an expert translator. The Arabic questionnaires will be back translated to English by another independent translator. The two translations will be checked independently by two bilingual investigators for accuracy of translation. Following content validity, field testing will be conducted on 20 women to inquire about the questionnaire’s clarity and ease of comprehension. Any concerns, comments or suggestions will be noted, and necessary changes will be made before generating the final Arabic B-KAB questionnaires. Test-retest reliability will be established using a group of 20 students. Pearson correlation coefficient > 0.7 will be considered acceptable. Validation of the Arabic versions will be tested on the first 200 subjects enrolled in the study.

b. *Breastfeeding pamphlet and Video:* At the end of each antenatal class, each subject in the intervention group will get an educational pamphlet and a video that contains information on breastfeeding benefits, techniques and expectations, as well as information on formula hazards. Subjects will be instructed to share both resources with their family members, particularly husbands, mothers and mothers-in-law.

2. Professional lactation support:

In order to improve their breastfeeding skills and self-efficacy, mothers in the intervention group will be visited on a daily basis by a trained lactation expert (professional lactation support) when admitted to the hospital for delivery. Visits will be 15–30 minutes long and will entail hands-on training on breastfeeding positioning and latch as well as breast care and common breastfeeding concerns. To ensure breastfeeding continuity after hospital discharge, mothers will be visited in their homes on days 1, 3, 7 and 15, and then monthly until the 6th month postpartum, breastfeeding discontinuation, or until the mother requests that they stop, whichever occurs first. The lactation expert will be provided with a telephone to provide a 24-hour hotline service for additional breastfeeding support, and will answer questions relating to breastfeeding or refer to a physician when appropriate.

3. Social network and social support:

To enrich a breastfeeding mother’s social networks and strengthen her social support, we will establish mother-to-mother networks intended to provide breastfeeding mothers in the intervention group (BFMi) with lay/peer support. Support mothers (SM) will be recruited via three different methods:

a. Enhancing existing social network linkages: Each enrolled participant will be asked to identify 1 – 3 women in her community or family whom she believes can serve as a source of support to her efforts to breastfeed successfully. Each BFMi will be asked to contact potential SMs and request they contact study recruiters for possible enrollment. Recruiters will receive potential SM calls and set a time and place to conduct an interview with the research team. During the interview, the mother-to-mother support program will be explained. Candidates possessing the necessary skills and willing to be support mothers will then sign a written informed consent and thus will be enrolled. Inclusion criteria of support mothers are: history of successful breastfeeding of at least one child for 2 months, positive feelings about breastfeeding, able to attend two half-day training sessions to learn how to support new mothers and when to refer to professional resources, and can read and write Arabic (middle school level).

b. Developing new social network linkages: Flyers inviting women to become support mothers will be posted on bulletin boards of AUBMC pediatric and obstetric clinics as well as SGH obstetric and pediatric clinics after their permission. Eligible candidates enrolled in this manner will be matched with intervention subjects who were not able to identify possible SMs in their community and/or those whose nominated candidates were not considered suitable by the research team. The matching process will be based on age, availability and geographical proximity. Similar to above, clinic patients who are interested in becoming support mothers will be referred to the research team by their primary care physicians.

c. Snowball effect: Each enrolled SM will be asked to identify 1 – 3 women in her community or family whom she believes could serve as a good source of breastfeeding support to other mothers. She would then ask her/them to contact study recruiters for possible enrollment and consent. After receiving the potential SM’s call, the recruiter will set a time and place to conduct the enrollment interview. During the interview, the mother-to-mother support program will be explained; candidates possessing the necessary skills and willing to be support mothers will be enrolled.

Using these methods, we hope to enroll close to 74 SMs or approximately 1SM for every 2–3 BFMi. Breastfeeding support will occur in an informal manner based on a minimum number of scheduled calls/visits as follows:

1. Face-to-face contact during first antenatal class

2. Telephone call at beginning of the 6th month of gestation

3. Telephone call at beginning of the 9th month of gestation

4. Telephone call during the expected week of delivery

5. Hospital visit on the first day postpartum

6. Home visit at/telephone call 48 hours from discharge

7. Home visit/telephone call at 1 week postpartum

8. Home visit/telephone call at 2 weeks postpartum

9. Home visit/telephone call at 4 weeks postpartum

10. Monthly home visits/telephone call till 6 months postpartum

Each BFMi will be given detailed instructions for contacting her SM when going to the delivery suite or immediately after delivery. Employed mothers who need to go back to their jobs after 4–6 weeks from delivery may be visited a week before the end of their maternity leave if they so wish. This schedule can be modified based on the needs of the BFMi. After each visit or call, support mothers will document details of the contact in the support mother activity record. Peer support will continue until the baby is 6 months of age or until the breastfeeding mother decides to stop, whichever comes first. Figure 1 details the flow of participants from recruitment till the last follow up contact for control and intervention subjects.

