#### Randomization

Eligible pregnant women will be randomly allocated to one of two parallel groups (experimental and control, 1:1 ratio), using a computer-generated stratified block randomization that is done by one of the co-investigators (HT) who is not involved in subject recruitment. The size of blocks will vary from 4 to 8 and the stratification will be by study site. Allocation concealment will be done to ensure that group assignment of the patients are revealed only after assessing the inclusion/exclusion criteria are verified and consent obtained. This will be done to avoid any bias that might be introduced by the investigator because of the knowledge of the next allocation group. A set of sequentially numbered opaque sealed envelopes will be prepared with the allocation group, as per the randomization list, specified inside.

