### Data collection

#### Participant mothers

1. *Baseline:* Age, socio-economic status, education, employment status, mother’s religion, baseline breastfeeding knowledge and attitude, parity, previous breastfeeding, baseline social support, study site, residence.

2. *Month 1:* Baby’s gender, mode of delivery, pediatrician’s gender, first feed at hospital, rooming in, breastfeeding status, baby’s illness visits (number, diagnosis, money spent on medicine and doctor’s fees), baby’s hospitalizations (number, diagnosis, cost), days lost from work due to baby’s illness, days lost from work due to mother’s illness, cost of formula feeds/week, cost of water used to prepare formula/week, mother’s non-routine doctor visits due to breastfeeding, cost of infant food/week, QoL.

3. *Month 3:* Breastfeeding status, baby’s illness visits (number, diagnosis, money spent on medicine and doctor’s fees), baby’s hospitalizations (number, diagnosis, cost), days lost from work due to baby’s illness, days lost from work due to mother’s illness, cost of formula feeds/week, cost of water used to prepare formula/week, mother’s non-routine doctor visits due to breastfeeding, cost of infant food/week, QoL.

4. *Month 6:* Breastfeeding status, baby’s illness visits (number, diagnosis, money spent on medicine and doctor’s fees), baby’s hospitalizations (number, diagnosis, cost), days lost from work due to baby’s illness, days lost from work due to mother’s illness, cost of formula feeds/week, cost of water used to prepare formula/week, mother’s non-routine doctor visits due to breastfeeding, cost of infant food/week, QoL, satisfaction of mother with mother-to-mother support system, breastfeeding knowledge and attitude of mother, in-depth interviews with BFMis.

5. *Year 1:* Breastfeeding status, baby’s illness visits (number, diagnosis, money spent on medicine and doctor’s fees), baby’s hospitalizations (number, diagnosis, cost), days lost from work due to baby’s illness, days lost from work due to mother’s illness, cost of formula feeds/week, cost of water used to prepare formula/week, mother’s non-routine doctor visits due to breastfeeding, cost of infant food/week.

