#### Process evaluation

During the support period, an ongoing evaluation process will take place in order to identify potential problems and implement changes accordingly. The process evaluation will ensure that the intervention is delivered and implemented as planned by evaluating the dose delivered, dose received, and reached.

The study research assistant will contact BFMis and SMs bi-weekly to inquire about the support process, including address potential complaints. The inquiry findings will be shared with the principal investigator within one business day. Process amendments and/or improvements will take place within the same week if necessary. In case of a perceived need for referral by SMs, physician members of the research team will be notified within the same day and will contact the BFMi-SM pair in question to evaluate and confirm the medical urgency and refer-or not- accordingly. At the end of the support period, all records are returned to the research team. When the latter receives the records, a post-support survey is sent to the breastfeeding mother to fill and return for data entry and analysis. Separate surveys will be sent to each support mother and to the professional nurses to assess their satisfaction. All BFMis will be contacted by the research team on yearly basis for 5 years after the trial ends to ask about their success in breastfeeding future babies. In addition, all mothers in the control group will be contacted by the research team at 1 month, 3 months and 6 months after delivery for data collection and outcome assessment similar to the intervention group. They will also be contacted on yearly basis for 5 years after the trial ends to ask about their success in breastfeeding future babies.

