### Statistical methods

We will compare continuous variables using Student’s *t* test and categorical variables using Chi square test. The relationship between breastfeeding exclusivity as outcome and the independent variables (maternal age, study group, socio-economic status, maternal education, study site, pediatrician’s gender, type of delivery, baby’s gender, parity, previous breastfeeding, maternal employment, mother’s religion, baseline breastfeeding knowledge and attitude, baseline social support) will be explored in bivariate and multivariate analysis. Regression models will be built to adjust for possible confounding in the relationship between the dependent and the independent variables stated above. All analysis will be done on intention to treat basis. The Statistical Package for Social Sciences (SPSS) will be used for data management and analyses. A p-value of <0.05 will indicate statistical significance.

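### Baseline knowledge, attitude and socio-demographic data are to be collected after allocation at intervention-only classes, yet serve as baseline covariates for both arms

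*Protocol article*

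**What the plan says.** All references are to the protocol article.

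- **Details of the complex intervention (antenatal classes).** Once enrolled and consented, "each subject in the intervention group will be invited to attend at least one antenatal session". The classes are "open to the intervention group only in order to avoid contamination with the control group". Socio-demographic data and "baseline breastfeeding knowledge, behavior and attitude towards breastfeeding will be collected at the beginning of each session from each subject". The instrument is the B-KAB questionnaire, whose Arabic version is to be validated on the first 200 women to enrol.
- **Randomization.** Assignments are "revealed only after assessing the inclusion/exclusion criteria are verified and consent obtained". No questionnaire is mentioned before that step.
- **Control group.** "Subjects in the control group will receive standard prenatal and postnatal care that is usually offered to mothers at both study sites".
- **Recruitment.** Recruiters approach women in the clinics, explain the study, check eligibility and obtain consent, with a private space for interviews. The section does not say that a baseline questionnaire is given there.
- **Data collection, Participant mothers, Baseline.** The list includes "baseline breastfeeding knowledge and attitude, parity, previous breastfeeding, baseline social support, study site, residence", with no restriction by arm and no time or place.
- **Process evaluation.** For data collection and outcome assessment, "all mothers in the control group will be contacted by the research team at 1 month, 3 months and 6 months after delivery", and yearly after that.
- **Statistical methods.** The independent variables in the exclusivity models end with "baseline breastfeeding knowledge and attitude, baseline social support) will be explored in bivariate and multivariate analysis". All analysis is by intention to treat.

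**The concern.** A baseline covariate in a randomised comparison should be measured before allocation, in the same way in both arms and in everyone randomised. The only collection procedure the article describes meets none of these conditions.

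A woman invited to an intervention-only class already knows her arm. Knowledge and attitude scores are self-reported, and hers would be given at a breastfeeding class to which family members are also invited. A control woman cannot be measured in that setting, so any value she has comes from a different one. An intervention woman who never attends has no described value at all.

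What is at stake is the adjusted analysis. If the model keeps only women with a recorded value, it can drop women from the intervention arm according to whether they took up the intervention. That runs against the stated intention-to-treat basis. If values exist in both arms but were obtained under different conditions, the model adjusts for something that allocation may itself have influenced.

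**Working it through.** **Order of events in the intervention arm, as described**
1. Eligibility is checked and consent obtained (Recruitment; Randomization).
2. Allocation is revealed (Randomization).
3. The woman is invited to a class for her arm only (Details of the complex intervention).
4. If she attends, the baseline data are collected at the start (same section).

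Step 4 follows step 2, so this baseline is post-allocation. If she does not attend, no route is described.

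**The same items by group**

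| Group | Measurement implied? | Time and place stated? |
|---|---|---|
| Intervention, attends a class | Yes | Yes: start of class, after allocation |
| Intervention, attends none | Yes, by the Data collection list | No |
| Control | Yes, by the Data collection list and the validation sample | No |

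Under 1:1 allocation, 200 consecutive enrolments would include about 200/2 = 100 controls, so the validation plan supports the middle column for controls. Baseline social support is listed and used as a covariate, but the sentence about the classes does not name it, so its timing is unstated in both arms.

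**The plan's own sample size** (Sample size section: 2% v 12%, 90% power, 5% type I error, 30% loss)
- Uncorrected, two-sided: n0 = [1.96·√(2·0.07·0.93) + 1.2816·√(0.02·0.98 + 0.12·0.88)]² / 0.10² = (0.7072 + 0.4535)² / 0.01 ≈ 134.7, or 135.
- Continuity-corrected: n = (n0/4)·[1 + √(1 + 4/(n0·0.10))]² = 33.68·(2.1388)² ≈ 154.1, or 155 per group, as stated.
- Total: 2·155/0.70 = 442.9, or 443, as stated.

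This point leaves those figures unchanged.

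**Illustration of selective loss.** The documents give no attendance rate, so the rates here are assumptions.
- About 443/2 ≈ 222 women per arm. If 20% never attend, 0.20·222 ≈ 44 have no described baseline; if 40%, 0.40·222 ≈ 89.
- Rough effect on precision: suppose all 155 followed-up controls are measured by some other route, only class attenders among 155 followed-up intervention women have a value, and the rates stay at 2% and 12%. With p̄ the pooled rate, power = Φ{[0.10 − ½(1/n1 + 1/n2) − 1.96·√(p̄(1−p̄)(1/n1 + 1/n2))] / √(0.02·0.98/n1 + 0.12·0.88/n2)}.
- Worked case, 80% attendance: n1 = 155, n2 = 124, p̄ = (3.1 + 14.88)/279 = 0.0644. The numerator is 0.0927 − 1.96·0.0296 ≈ 0.0348, the denominator is 0.0313, and Φ(1.11) ≈ 0.87.

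| Assumed attendance | Intervention women with a value | Power |
|---|---|---|
| 100% | 155 | 90% |
| 80% | 124 | 87% |
| 60% | 93 | 81% |
| 50% | about 78 | 77% |

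This is a two-proportion approximation, not the adjusted model itself. It shows lost precision only. Any bias from dropping non-attenders is additional and cannot be sized from the documents.

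**The case against.** The strongest reply is that the sentence about the classes only describes what happens at a class and was never meant as the sole collection route. The dedicated data-collection section lists the items for participant mothers in general, validation uses the first women to enrol whatever their arm, and Recruitment gives every woman a private contact before allocation. The flow diagram is not shown, and the article condenses a fuller protocol; either might place a baseline assessment for controls. This stands to a large extent, and it rules out several stronger conclusions that a reader might infer:

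- **That half the trial has no baseline data and the adjusted model cannot be fitted.** This follows only if the class is the sole route, which overrides the Data collection list.
- **That controls are first seen one month after delivery.** Process evaluation is not a complete visit schedule, and the recruitment contact precedes allocation.
- **That the knowledge and attitude outcome loses the protection of randomisation.** Secondary outcome (c) is a between-arm comparison at 6 months and needs no baseline value.
- **That the primary result is compromised.** The chi-square comparison of 6-month exclusivity does not use the covariate.
- **That women are re-measured after teaching.** Appendix A describes a single one-hour session, and the wording most naturally means each class with its own attendees.
- **That those who stay away are the less motivated.** This is plausible, but the documents say nothing on it.

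It is also fair that age, education, parity and religion cannot be altered by allocation, that the models are described as exploratory, and that handling of missing covariates is usually left to the analysis plan.

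The reply does not remove the instruction itself. The article states a procedure, and it is a post-allocation one in the intervention arm. Measuring controls elsewhere would still leave the arms unlike in setting and leave non-attenders without a described value, including for the fixed characteristics.

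**Conclusion.** The point holds in a limited form. The sections on the antenatal classes and on data collection do not agree about when and from whom baseline data are taken. If the stated procedure is followed, the baseline knowledge and attitude covariate is measured after allocation in the intervention arm, is not comparable with any control value, and is undescribed for intervention women who attend no class.

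The damage is confined to the adjusted exclusivity models and to any change-from-baseline analysis of knowledge and attitudes. Its size is unknown. The figures of 44–89 women, and power of 87% to 81%, depend on assumed non-attendance of 20–40%, on a complete-case analysis, and on non-attenders having no value from another source. The sample size is unaffected.

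It is worth settling before enrolment because a measurement not taken before allocation cannot be recovered at analysis.

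**What to change.** Reconcile Details of the complex intervention with Data collection. State that the socio-demographic, social-support and B-KAB baseline questionnaires are given to every woman in both arms at the recruitment interview, after consent and before her allocation envelope is opened. Remove baseline collection from the antenatal classes. If a questionnaire is kept there, label it a process measure and state that it is not used as baseline in any analysis.

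The cost is a sentence or two in the protocol and a slightly longer enrolment visit. The questionnaire is already planned, and a private interview space is already provided in each clinic. The sample size and the primary analysis stay as they are.
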